**Fig. 1 Fig1:**
[figure not shown]
CONSORT for mhGAP/IPT-G Randomized Pilot Feasibility Study

**Table 1 Tab1:** Summary table the pilot feasibility trial

Objectives	Outcomes	Criterion for success	Method for analysis	Estimate of effect
Primary feasibility	Demonstrate that the method of RCT feasible in MCH clinical service context	70% of pregnant adolescent-caregiver-health care workers that are exposed to content of the intervention; 80% of data collection performed as planned;	Quantitative analysis for implementation outcomes will be based on data collected throughout the implementation period, and analyzed separately for each time point as well as jointly to create overall summary scores. Analysis for the MCH service outcomes will be based on pre-post intervention data using pair-t tests and repeated measures. Quantitative data for implementation outcomes, MCH service outcomes, and adolescent mental health effectiveness outcomes will be examined separately. Qualitative data will be transcribed and analyzed using similar techniques described in Aim 1. We will review all focus group discussion data and use grounded theory approach to search for emerging themes using open and axial coding.	Depression and family functioning will be based on multi-level modeling, adjusting for family/group nesting effects. Post-intervention effects estimated as a function of baseline levels of the corresponding outcome variables and intervention status.
Secondary outcomes	a) Identification of barriers and facilitators to mhGAP/IPT-G implementation in MCH context b) Capacity building of MCH personnel, researchers and select MOH and County health partners c) Adaptation of mhGAP/IPT-G	a. Identification of select mhGAP informed barriers to care and adaptation of mhGAP and IPT-G for this context b. Capacity building will significantly improve trainees’ (nurses and community health workers) knowledge and skills in implementation research and delivering of depression intervention. c. Adapted manual for IPT-G and algorithm for mhGAP-IG for depression for pregnant adolescents	Qualitative and ethnographic methods including mixed methods using D& I and attitudes to EBI and adolescent friendly health services Pre and post training interviews and acceptability and satisfaction the trainings Knowledge and fidelity trainings on mhGAP/IPT-G	N/A

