**Table 2 Tab2:** Study measures for the feasibility evaluation study: constructs, informants, assessment schedule, and assessment tools (to accompany the SPIRIT figure)

Constructs, informant, & assessment time	Assessment tools/measures
**Multi-level D&I Context (domains listed in** Fig. 1**)** [Time 1]	
**Inner setting &Individual Characteristics (MCH staff, Adolescent reports)):** * MCH system characteristics; * Implementer demo & attitude about the EBI; * Family characteristics	Provider Environment Questionnaire Survey [45, 47]; Organization climate/Readiness Questionnaire [47]; EBP Attitude Scale [46]; Family Demographics /Social determinants
**mhGAP/IPT-G Implementation Feasibility Outcomes** [Assessed Throughout Implementation Period]	
**a) Fidelity (Staff):** Feasibility in implementing mhGAP service delivery model and delivering > 80% of session content in MCH setting; **b) Engagement (staff report)**: Feasibility in reaching the targeted population (adolescent-parent pairs), and maintain high program participation/session attendance; **c) Quality of Implementation (adolescent-report)**: *****Acceptability, Appropriateness Usefulness, Satisfaction (of IPT-G implementation procedures and contents);	**a**: Fidelity Checklists **b:** Program Engagement, attendance; **c.** Acceptability, Appropriateness, Usefulness, Satisfaction;
**MCH Mental Health Service Outcomes** [Time 1, Time 2]	
**a) MCH service quality (adolescent mothers):** patient satisfaction of the integrated mental health & MCH care**;** **b) MCH climate (staff & adolescent report)**: support, trust, communication about adolescent health; responsive adolescent services.	**a:** Service quality; **b:** Organization Climate Questionnaire [47]
**mhGAP/IPT-G trial design feasibility and effect size estimation for mental health & family functioning outcomes** [Time 1, Time 2]	

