#### Intervention implementation

Participants will be randomly assigned to IPT-G Full, IPT-G Mini, and wait-list control using computer random generator by research staff (*n* = 15 for each arm, 45 per cohort).
The IPT-G Full and Mini groups will receive the assigned interventions (8 vs. 4 sessions) developed from Aims 1 and 2 (including a perinatal depression educational material/handout). To avoid contamination, intervention for the IPT-G Full and Mini versions will be carried out by 2 separate implementation teams (2–3 facilitators in each team) follow the assigned manual/protocol. Figure 2 provides intervention contents for the Mini version, in comparison to the recommended Full version.The Control will receive standard care (with referral) and perinatal depression educational materials for safety concerns. They will receive IPT-G Mini after the post implementation assessment is completed.

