#### Feasibility evaluation measures and procedure

To evaluate feasibility of the mhGAP-IG/IPT-G implementation model in the MCHs, a mixed methods data collection approach will be applied and data will be collected from multiple sources (i.e., implementers, MCH leaders, adolescent mothers and their family members) to minimize data collection bias. As described above, the *Conceptual model of Implementation Outcomes* [56] is applied to guide the construct selection for the implementation feasibility and impact estimation. Feasibility of the mhGAP/IPT-G mental health service delivery model will be assessed using three indicators: fidelity (i.e., % of sessions is delivered with > 80% of contents), level of engagement (e.g., % reach targeted population, % participating in intervention sessions), quality of implementation (e.g., acceptability, appropriateness, usefulness, satisfaction of the mhGAP/IPT-G service model), and perceived mental health service (e.g., mental health service quality, MCH climate). Feasibility of applying a trial design for mhGAP/IPT-G impact evaluation in MCHs will be assessed using two indicators: % of adolescent-caregiver pairs that are exposed to intervention contents within the assigned condition; and % of data collection performed as planned. Impacts/effect size estimation for the IPT-G Full and Mini versions (the secondary outcomes) will be assessed for adolescents’ mental health and family functioning outcomes. Both quantitative data and qualitative data will be collected. Qualitative data will be collected through focus groups (2 groups for each intervention arm) at the end of implementation cycle. Tables 1 and 4 lists the feasibility outcomes measures and sources of data collection (under implementation feasibility, mental health service outcomes, and trial design feasibility and effect size estimation). Implementation feasibility outcome data, collected from the MCH staff/intervention implementers and adolescents who participated in the two intervention arms (IPT-G Full and Mini), will be gathered after each group session throughout the two implementation periods. For effect-size estimation, all study participants will complete a baseline (Time 1) interview (on mental health and family functioning outcomes) before randomization and intervention implementation, followed by a 1- or 2-month implementation period (2 months for the IPT-G Full and 1 month for the IPT-G Mini). Only when a participant is physically unwell, or has to terminate due to a pregnancy related emergency or any other severe mental health issue will their participant grouping be unblinded and an appropriate referral made. They will receive a post-intervention interview assessment at the end of implementation cycle (Time 2, about 3–4 months after the Time 1). To facilitate coordination of program implementation activities, participating MCH will be provided with two tablets and a small incentive which could offset implementation costs.

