#### Analysis plan for the feasibility outcomes

Data collected through 2 cohorts will be analyzed. Quantitative analysis will be focused on examining the following questions:
Examine acceptability, appropriateness, usefulness, engagement, and fidelity for both full and mini versions of integrated mhGAP/IPT-G intervention implementation using task-shifting/sharing approach in MCH contexts.Examine MCH service quality change patterns before and after implementation of the mhGAP/IPT-G model will improve.Examine whether pregnant adolescents in the IPT-G will have better outcomes relative to control, but high impacts/effect size for the IPT-G Full version.

The following stop-go criteria will be used to determine whether to proceed to the main trial: the recruitment proceeds well so that the first IPT-G cohort can proceed by the end of the first month of the specified recruitment period. The IPT therapists that is the trained CHVs and nurses demonstrate adequate levels of treatment fidelity to the WHO IPT-G checklist adherence available in the manual and 70% of participants attend at least 5 of the available sessions in the course of their treatment and 80% are successfully followed up at primary endpoint.

Quantitative analysis for *implementation outcomes* will be based on data collected throughout the implementation period, and analyzed separately for each time point as well as jointly to create overall summary scores. Analysis for the *MCH service outcomes* will be based on pre-post intervention data using *paired-t tests* and repeated measures. We will examine patterns separately and jointly for two MCH clinics. Analysis for *estimating size of impact* on mental health (depression) and family functioning will be based on multi-level modeling, adjusting for family/group nesting effects. Post-intervention effects/impacts will be estimated as a function of baseline levels of the corresponding outcome variables and intervention status. Effect size (regardless the statistical testing significant level) will be computed. *Quantitative data* for implementation outcomes, MCH service outcomes, and adolescent mental health effectiveness outcomes will be examined separately.

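### Adolescent-rated MCH service quality and climate are to be tested before against after with no arm term, although the trial has a randomised wait-list control

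*Protocol article*

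**What the plan says.** Table 1 gives the method: "Analysis for the MCH service outcomes will be based on pre-post intervention data using pair-t tests and repeated measures". The section Analysis plan for the feasibility outcomes repeats it, adds that the two clinics will be looked at separately and together, and mentions no breakdown or model term for arm. The question it is meant to answer is worded: "Examine MCH service quality change patterns before and after implementation of the mhGAP/IPT-G model will improve".

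Table 2 lists the outcomes. Service quality is reported by adolescents and described as "patient satisfaction of the integrated mental health & MCH care". Clinic climate is reported by staff and adolescents. Both are measured at Time 1 and Time 2, with no limit to particular arms.

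On timing, Feasibility evaluation measures and procedure says that "all study participants will complete a baseline (Time 1) interview (on mental health and family functioning outcomes) before randomization and intervention implementation". Time 2 comes at the end of the implementation cycle, about three to four months later.

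On the control arm, Intervention implementation says: "The Control will receive standard care (with referral) and perinatal depression educational materials for safety concerns". It continues: "They will receive IPT-G Mini after the post implementation assessment is completed".

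For mental health and family functioning, the same analysis plan takes another route: a multilevel model of the Time 2 value on its baseline and on intervention status.

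**The concern.** A paired test asks whether the mean changed, not why. Over three to four months of antenatal visits an adolescent's rating of a clinic can move for reasons unrelated to mhGAP or IPT-G, such as growing familiarity with staff, advancing pregnancy or a change in what she expects. The stated question anticipates improvement, so a significant paired test would naturally be read as showing that the model improved the service.

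The trial already has the means to check this. It randomises a group that has had no IPT-G by Time 2, and it already specifies an arm comparison adjusted for baseline for its clinical outcomes. For service outcomes that comparison is not named. What is at stake is an unsupported claim about service quality in the pilot report.

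**Working it through.** **Sample size.** Intervention implementation gives 15 per arm per cohort, three arms and two cohorts: 15 × 3 × 2 = 90, which agrees with the Sample size section. That is 30 per arm, so 60 adolescents receive Full or Mini. The document gives no alpha, SD, correlation, effect size or power for service quality. The following are therefore assumptions: two-sided alpha 0.05, pre-post correlation ρ from 0.3 to 0.7, and a drift d of 0.2 to 0.5 SD shared by all arms, with no intervention effect. Nesting in therapy groups is ignored.

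**Paired t-test.** In units of the outcome SD, the SD of change is √(2(1 − ρ)). The noncentrality is d√n / √(2(1 − ρ)), with n − 1 degrees of freedom. At ρ = 0.5 the SD of change is 1. For d = 0.3 the noncentrality is 0.3 × √60 = 2.32 with the treated arms only, and 0.3 × √90 = 2.85 with everyone. Rejection rates from the noncentral t:

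| n | ρ | d = 0.2 | d = 0.3 | d = 0.5 |
|---|---|---|---|---|
| 60 (treated) | 0.3 | 25% | 49% | 90% |
| 60 | 0.5 | 33% | 63% | 97% |
| 60 | 0.7 | 50% | 84% | 99.8% |
| 90 (all) | 0.3 | 36% | 66% | 98% |
| 90 | 0.5 | 47% | 80% | 99.7% |
| 90 | 0.7 | 68% | 95% | about 100% |

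With d = 0 every row is 5%. A simulation of 20,000 trials with n = 60, d = 0.3 and ρ = 0.5 gave 62.3%, in line with the 63% above.

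**Baseline-adjusted arm comparison.** If the drift is the same in every arm, Time 2 = d + ρ × Time 1 + error in each arm. The drift goes into the intercept and leaves the arm coefficient untouched. The same simulation, comparing 60 treated with 30 controls, rejected in 4.8% of trials.

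**Power of that comparison.** At ρ = 0.5 the residual SD is √(1 − 0.25) = 0.866.

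- 60 v 30: SE = 0.866 × √(1/60 + 1/30) = 0.194. Power is about 34%, 73% and 98% for true differences of 0.3, 0.5 and 0.8 SD.
- 30 v 30 (one version against control): SE = 0.866 × √(2/30) = 0.224. Power is about 27%, 61% and 95%.

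**The case against.** There is a fair case on the other side, and parts of it stand.

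- **The question is about the service model, not about arms.** The plan asks about change before and after implementation. The Abstract places all three arms, wait-list included, within mhGAP care, while Intervention implementation gives the control standard care with referral. If mhGAP care reaches every arm, a comparison with control isolates the IPT-G sessions and cancels any clinic-wide effect. Staff have no arm at all. This stands: the arm comparison belongs beside the before-after figures and cannot replace them.
- **Repeated measures could include arm.** Such a model can carry an arm-by-time term, and a condensed article may leave model terms to a fuller plan. But arm is named for the mental health outcomes and only clinic is named here, and the paired t-test, which is named, cannot carry an arm term.
- **Controls may not answer these items.** A reader might infer that they do and that all 90 will be pooled. Neither is stated. The sentence about all participants concerns mental health and family functioning; for service items there is only the absence of an arm limit in Table 2. The problem does not depend on pooling, since the 60 treated alone show it.
- **The Time 1 rating.** A reader might infer that it rates nothing, because integrated care has not begun. That reads too much into one table entry: the item wording is not shown, and the adolescents could rate the existing MCH care. The label needs clearing up; the measure is not void.
- **Importance.** The method sits in the primary feasibility row of Table 1, so a reader might infer that it bears on whether to proceed. The note to Table 2 ranks service outcomes as intermediate or secondary, and neither the Table 1 success criteria nor the stop-go criteria use them.

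**Conclusion.** The concern holds for adolescent-reported service quality and climate. As written, the plan names a test that cannot distinguish an effect of the model from change over time, and it does not name the randomised comparison that could remove shared drift. At ρ = 0.5, with no intervention effect, the paired test would declare a change in roughly 33–97% of trials (60 treated) or 47–99.7% (all 90) for drifts of 0.2–0.5 SD, against about 5% for the adjusted arm comparison. Drift and correlation are assumed. No single percentage should be read as the trial's false-positive rate, and with no drift the paired test is sound at 5%.

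The point is about interpreting a secondary pilot outcome. It does not undermine the decision to proceed to a main trial, and it does not make the before-after question wrong to ask.

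**What to change.** 1. State that the adolescent service-quality and climate items are collected at Time 1 and Time 2 in all three arms.
2. Word the Time 1 satisfaction item as satisfaction with the MCH care currently received.
3. Add a Time 2 comparison of Full and Mini with control, adjusted for the Time 1 rating and clinic, using the multilevel model already stated for mental health outcomes, with its allowance for group nesting.
4. Report before-after change by arm and clinic, and all staff-reported change, as estimates with 95% confidence intervals and no claim that the model caused it.

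The cost is analysis wording, one item's wording and, if controls were not already due to answer, a few more questions at interviews they attend anyway. No participants or visits are added. There are two downsides. The arm comparison speaks to IPT-G and not to clinic-wide mhGAP change, so the latter appears only in the descriptive figures. Its power is also modest (for 60 v 30 at ρ = 0.5, about 34% at 0.3 SD and 73% at 0.5 SD, before any loss from nesting), so it should be presented as an estimate with its interval.

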## Conceptual model and design overview

### Conceptual model

The adaptation, implementation, and evaluation of the mhGAP/IPT-G will be guided by an integrated conceptual model that combines two dissemination and implementation (D&I) frameworks. D&I research is a growing field that informs how evidence-based interventions and practices can be successfully adopted, implemented, and maintained in health care delivery and community settings. Its methods and frameworks provide guidance around building teams, engagement with stakeholders, maintaining fidelity and adapting tools and interventions to varied cultural and organizational settings [48]. The *Consolidated Framework for Implementation Research (CFIR)* [48, 49], which accounts for five domains of contextual factors that may influence key determinants that impact implementation and effectiveness outcomes, will be used to guide implementation and adaptation strategy development under aims 1 & 2. The five major domains of the CFIR include the *intervention, individuals involved*, *the inner* (including political, structural, and cultural contexts) and *outer* (including social, economic, and political contexts) *settings*, and *the process by which implementation is accomplished*. The *Conceptual model of Implementation Outcomes* [56], which provides a framework for guiding implementation, service feasibility, and effect size/impact estimation, will be applied to guide the aim 3 outcome estimation. Applying both multi-domain/level D&I frameworks will result in: (1) improved strategies to address knowledge gaps toward adolescent friendly and family-centered adolescent pregnancy and mental health care; (2) identification of low-cost support strategies from health care workers, family members and community to support the adolescent; (3) engaged/motivated strategies for adolescents toward making proactive behavioral and health changes (i.e., for promoting their reproductive health and wellbeing); (4) integrated quality MCH services supported by local providers and policy stakeholders; and (5) evidence for effective mhGAP/IPT-G implementation and potential efficacy outcomes.

### Design overview and setting of the study

A rigorous mixed methods study will be used to study strategies to adapt and improve mhGAP-IG and IPT-G for Kenyan adolescent population and MCH implementation contexts. The pilot implementation study will be based at two Nairobi primary health care centers—Kariobangi North and Kangemi. Kariobangi is a low-income residential estate in north eastern part of Nairobi, Kenya. Kariobangi consists of both lower middle class and slum-type dwellings and is split into two parts: Kariobangi North and Kariobangi South. Kariobangi North is located approximately 15 kms from Nairobi city center. Kariobangi north is estimated to have 8000 to 10,000 residents. Kangemi is a slum in Nairobi County located in a small valley on the outskirts of the city. It is bordered on the north by the middle-class neighborhoods of Loresho and Kibagare and Westlands on its west. Different sources report that Kangemi has more than 100,000 residents. The study will be conducted in Nairobi at the Nairobi County’s two primary health care facilities that offer MCH services. The study is conducted in collaboration among partners from the University of Nairobi, Ministry of Health (Community Health Promotion and Mental Health Departments), WHO non-communicable diseases unit, and UNFPA’s adolescent SRH section. After enrolment, adolescents will be followed through regular clinic visits in the two respective centers. The study clinic will have dedicated staff including clinical and nursing officers able to provide clinical care offered as part of routine Antenatal Clinic (ANC) care for pregnant adolescents. The assumption is that the pregnant adolescent will seek the intervention and ANC at the clinic site from where she was recruited. The delivery options might vary depending on the personal situation, obstetric history and medical complications associated with pregnancy. However, the participants will be tracked on the delivery and birth outcomes wherever childbirth takes place.

Kenyatta National Hospital/University of Nairobi ethics review committee has approved the study and additional approvals were sought from Nairobi county health directorate and National Commission for Science, Technology and Innovation which will be renewed annually (as per the respective committee policies).

## Methodology

Figure 1 provides an overview of the study procedure and design for the pilot randomization trial. Below we provide detailed methodological approach for the pilot feasibility trial and the two sub-studies.

### Methodology for primary pilot trial

Considering high prevalence of adolescent pregnancy, high risk for depression in this population, and low resource in MCH clinics, the WHO recommended Full version of IPT-G may not be practical in meeting population service demands and needs. Therefore, we will test a Mini version of IPT-G in comparing to the Full version of IPT-G in the context of mhGAP mental health service delivery model. For this Aim, our primary goal is to evaluate the feasibility of implementing the integrated mhGAP-IG/IPT-G service model in the MCH contexts as well as feasibility of applying RCT design to study differential impacts of the IPT-G Full and Mini version in MCHs. Our secondary goal is to estimate the sizes of effect for the mhGAP/IPT-G Full and Mini versions.

